### Statistical analysis

Intention to treat analysis will be used.

Categorical variables are compared using a chi-square test, and the Student t-test is used to compare continuous variables between groups. Logistic regression with adjustment for other possible risk factors for meningitis is used to estimate the odds ratios and 95% confidence intervals.

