With this concept in mind, the authors tried to clarify those subgroups at risk in two subsequent studies since 1994. In the first study done in our hospital ([name], [name], [name], unpublished data), the efficacy of prophylactic antibiotics in head injury patients with skull base fracture were studied. Although no statistically significant differences were found between those with and without prophylactic antibiotics, 12% of patients with skull base fractures had pneumocephalus and the incidence of meningitis was considerably higher (20%) in this subgroup of the head injury patients. In the second study we selected only patients with posttraumatic pneumocephalus. The overall meningitis rate in head injury patients with pneumocephalus was 21.5% [5]. That study again did not approve the prophylactic administration of ceftriaxone (2 grams daily) in the pneumocephalus patients. But it showed that CSF rhinorrhea and intracranial hemorrhage might be considered as primary risk factors and in the absence of them, intradural location of air and air volume greater than 10 cc as secondary risk factors for developing meningitis in posttraumatic pneumocephalus patients [5]. Even in those patients with CSF rhinorrhea or intracranial hemorrhage, prophylactic ceftriaxone (2 grams daily) did not prove to be effective on prevention of meningitis.

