### Sample size

The frequency rate of meningitis among our traumatic pneumocephalus patients was 21.5% (*p*1). What we expect to be an intended (or at least acceptable) effect of the prophylactic antibiotics is 5 %(*p*2) frequency of meningitis in the patients with antibiotics. To detect this difference with a sensitivity of 80% and an error probability of 5%, at least 62 patients per randomization group will be required using the following formula:

*n *= 7.84 * [*p*1(1 - *p*1) + *p*2 (1 - *p*2)]/[*p*_1 _- *p*_2_]^2^

Considering only comparing the placebo group with each one of the antibiotics group, our sample size should be at least 186 cases. To account for the possibility of loss to follow-up, our estimated sample size is 200 cases.

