### Study design

The patients should be observed in the hospital, until occurrence of meningitis or at least 7 days after trauma. In the case of concomitant Cerebrospinal Fluid (CSF) leakage and need for close observation in the hospital, they will be hospitalized until recovery from leakage. After discharge the patients will be followed up until one month after trauma.

The following data is registered: age, sex, time interval between trauma and admission, time interval between admission and antibiotic therapy, the cause of trauma, GCS upon admission, intracranial air volume (at the time of admission and three days later), intracranial air location, presence of CSF rhinorrhea, CSF otorrhea, presence and location of the radiological signs of skull base fractures, presence and volume of the intracranial hemorrhage(at the time of admission and three days later), presence of meningitis, CSF findings, treatment and complications in the case of meningitis and one month follow-up note.

Intracranial air and hemorrhage volume are calculated in the CT scan using the formula *ABC*/2, where *A *is the greatest mass diameter by CT, *B *is the diameter 90° to *A*, and *C *is the approximate number of CT slices with mass multiplied by the slice thickness. In the case of air in the subarachnoid space, this formula is not easily applicable and an approximate volume is calculated and determined whether the volume is less than 10 cc or not [7].

The patients are divided into three groups; with intravenous antibiotics (IV), oral antibiotics (O) and placebo (P), according to the randomization list. In IV group, Ceftriaxone 2 grams BID plus oral placebo and in O group, Azithromycin 500 mg in the first day followed by 250 mg daily plus intravenous placebo for the rest will be continued for 7 days. Antibiotics should be started in less than 24 hours after trauma. Since antibiotics may mask the clinical presentation of the meningitis, these patients (IV and O) will remain hospitalized two more days for close clinical observation. In the case of meningitis, appropriate antibiotics are continued until patients' recovery. Corticosteroids should not be prescribed for the patients for any reason.

The physicians caring for the patients are not blinded to the regimen that is used.

Intracranial hemorrhages included subarachnoid hemorrhage, epidural and subdural hematoma and cerebral contusion or hematoma.

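### With about 21 meningitis events expected, ordinary adjusted logistic regression is likely to push the odds ratios away from 1 and will sometimes give none; a penalised fit on a short list of admission covariates is better

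*Protocol article*

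**What the plan says.** The Statistical analysis section of the protocol article names a chi-square test for categorical variables and a t-test for continuous ones, and then states: "Logistic regression with adjustment for other possible risk factors for meningitis is used to estimate the odds ratios and 95% confidence intervals". This is the only effect estimate with a confidence interval in the article.

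The Background reports from the group's earlier study that "CSF rhinorrhea and intracranial hemorrhage might be considered as primary risk factors". Where both are absent, it names intradural air and an air volume above 10 cc as secondary factors. Those are four named risk factors in all.

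The Sample size section supplies the planning figures. It states "The frequency rate of meningitis among our traumatic pneumocephalus patients was 21.5" per cent, and expects a 5% "frequency of meningitis in the patients with antibiotics". From these it concludes: "To detect this difference with a sensitivity of 80% and an error probability of 5%, at least 62 patients per randomization group will be required". The total follows ("our sample size should be at least 186 cases"), and then the allowance for losses: "To account for the possibility of loss to follow-up, our estimated sample size is 200 cases". The Randomization section gives three groups in permuted blocks of three, so allocation is equal.

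**The concern.** The information in a logistic model is limited by the number of events, not the number of patients. If prophylaxis works as planned, the trial will have few events, and very few in the two groups whose odds ratios matter most. Maximum-likelihood odds ratios are then biased away from 1. An odds ratio has no finite value at all if an antibiotic group has no meningitis.

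Both problems are worst when the drugs work, which is the situation the trial is sized to detect. The bias would overstate the benefit of antibiotics in the one estimate reported with a confidence interval.

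**Working it through.** **Inputs.** From Sample size: p1 = 0.215, p2 = 0.05, N = 200 (minimum 186). From Randomization: three equal groups. From Background: four named risk factors. Two treatment terms follow from having three groups.

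**The plan's own figure.** n = 7.84 × [0.215 × 0.785 + 0.05 × 0.95] / (0.165)² = 62.28. This reproduces the stated 62 per group (63 if rounded up).

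**Expected events.** Events = N/3 × (p1 + 2 × p2).
- N = 200: 66.7 × 0.315 = 21.0, made up of 14.3 on placebo and 3.3 on each antibiotic. The simulated 95% range is 13 to 29.
- N = 186: 62 × 0.315 = 19.5.
- N = 200, one regimen works: 66.7 × (2 × 0.215 + 0.05) = 32.
- N = 200, neither works: 200 × 0.215 = 43.

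**Events per parameter at 21 events.** Treatment terms only: 21/2 = 10.5. With the four named factors: 21/6 = 3.5. With four further registered factors (age, GCS, skull base fracture, otorrhea), as an illustration only: 21/10 = 2.1.

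**Chance of an empty antibiotic group.** For one group of 66: 0.95^66 = 0.034. For at least one of two: 1 − (1 − 0.034)² = 0.067. At N = 186: 0.95^62 = 0.042, and 0.081 for at least one of two.

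**Simulation.** There were 2,000 trials per row. Covariates were independent and binary, and their prevalences and effects are assumptions, not figures from the protocol. Prevalences were 0.3, 0.5, 0.5, 0.4 for the first four and 0.3, 0.2, 0.5, 0.5 for the rest. Log odds ratios were 1, 1, 0.5, 0.5 and then 0.3, 0.3, 0, 0. Rates were calibrated to the planning values. Bias and coverage for each method are over trials with a finite fit by that method. Coverage uses Wald intervals.

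| Model | Mean events | No finite ML fit | ML mean log OR ÷ true | ML median OR (true) | ML coverage | Firth mean log OR ÷ true | Firth coverage |
|---|---|---|---|---|---|---|---|
| Treatment only | 21.0 | 6.8% | 1.03 | 0.195 (0.192) | 97.0% | 0.99 | 96.1% |
| + 4 covariates | 21.0 | 6.2% | 1.08 | 0.156 (0.173) | 97.8% | 1.00 | 96.5% |
| + 8 covariates | 21.0 | 7.5% | 1.13 | 0.144 (0.172) | 97.5% | 1.00 | 96.0% |
| + 8 covariates, N = 186 | 19.5 | 9.3% | 1.12 | 0.147 (0.172) | 97.1% | 0.99 | 95.9% |

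With no treatment effect (43 events, eight covariates), every ML fit was finite, the mean log OR was −0.01 and coverage was 95.0%.

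Two further simulations under other assumed covariate effects agree in direction:
- One, with eight covariates, gave a mean ML log OR of −2.10 against a true −1.82 (ratio 1.15; OR 0.12 against 0.16), no finite fit in 9.75% of trials, and a Firth mean of −1.84.
- The other gave inflation of about 9% with the four named factors and about 12% with eight covariates, and no finite ML fit in 6 to 8% of trials. Firth was always finite and within about 2% of the truth.

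**The case against.** The strongest objection is that the article specifies no model. It does not say that all risk factors enter, gives no number of parameters, and does not exclude a short list or a penalised fit. A condensed article may leave the covariate list to a fuller document. That stands: the missing list is not a fault, and a ten-parameter model is only an illustration of where open-ended adjustment could lead. But the low count in the antibiotic groups follows from the planning rates whatever the list. Ordinary logistic regression already fails in 6.8% of simulated trials with no covariates, and it shows the bias with just the four factors the article names.

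Other parts of the objection also stand:
- Failure to fit comes mainly from an empty antibiotic group. It hardly changes with the number of covariates (6.8%, 6.2%, 7.5%), so trimming the list alone would not cure it.
- The 21 events assume that both regimens reach 5%. With 43 events there was no material bias. The Background reports no proven benefit of ceftriaxone at a lower dose, so that case is realistic.
- ML intervals over-covered slightly, so the harm is to the point estimate rather than to coverage.
- The article does not call the adjusted odds ratio primary. The frequency of meningitis can be compared by the chi-square test, which this point does not touch.

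A reader might also infer that the model will adjust for values measured after treatment starts, because the Study design section registers "intracranial air volume (at the time of admission and three days later", and likewise for hemorrhage. The article does not say that the later values enter the model, and admission values exist for both. Restricting covariates to admission is a sensible safeguard, not the correction of a stated error.

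**Conclusion.** The point holds in a limited form. At the planning rates, about 20 to 21 events give roughly 3.5 per parameter with the four named factors, and fewer if more are added. ML odds ratios are then likely to be biased away from 1, by roughly 8 to 15% on the log scale with four to eight covariates, and to have no finite value in roughly 6 to 10% of trials.

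For scale, the large-sample standard error of the unadjusted log OR at the expected counts is √(1/14.3 + 1/52.3 + 1/3.3 + 1/63.3) ≈ 0.64. The bias is about 0.14 (0.082 × 1.75) with four covariates and up to 0.28 (2.10 − 1.82) with eight. It is systematic and flatters the antibiotics, but it is smaller than the sampling error.

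The event count and the chance of an empty group rest on the protocol's figures alone. The bias also depends on the assumed covariates; rarer or stronger ones would make it worse. A stronger reading, that the odds ratios will be exaggerated or cannot be estimated, is not supported: over 90% of simulated trials gave finite fits, and the problem is small if neither regimen works. This is an inexpensive improvement to the analysis and not a flaw that invalidates the trial.

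**What to change.** In the Statistical analysis section:

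1. Fit the adjusted model by Firth's penalised likelihood with profile-likelihood confidence intervals. This is the step that deals with an empty antibiotic group.
2. Prespecify a short covariate list, measured at admission and drawn from the Background: CSF rhinorrhea and intracranial hemorrhage, with air location and air volume above 10 cc at most. Keep models with other risk factors exploratory.
3. Report alongside it the unadjusted risk difference with 95% confidence interval for each antibiotic group against placebo. This can be given even when a group has no events, provided the interval method suits small counts (a score-based one, for example).

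The cost is a change of wording and the use of standard software; design, sample size and data collection stay as they are. The downside is slightly less adjustment for minor factors and slight shrinkage of the estimates. In the simulations the Firth median OR was 0.183 against a true 0.173 with four covariates, although its mean log OR was on target.

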## Discussion

This study can be a major step forward solving one of the controversial issues in the management of traumatic pneumocephalus. Considering our circumstances the design of the study is not double-blinded. This may be one of the potential shortcomings of the study.

## Conclusion

In conclusion, this study is aimed to study the effectiveness and indications of prophylactic antibiotics in prevention of meningitis in traumatic pneumocephalus patients after mild head injury.
